### Participant timeline

4.3

Enrolled participants follow a sequence of screening, baseline intervention and follow up. During the initial screening (Week 0), the medical officer document demographic details, perimenopausal status (STRAW staging), and chronic insomnia symptoms which is occurring at least three nights per week for the past 3 months. Screening evaluations will include the Insomnia Severity Index (ISI) to determine eligibility, PHQ-9 to rule out depressive symptoms (≤5), review of recent medication use, and assessment of BMI (≤35). Baseline medical history, lifestyle factors (sleep schedule regularity, shift-work exclusion), and technology readiness (phone/internet access) will be verified. *Prakriti* (constitutional profile) assessment and documentation of baseline *Dosa dushti lakshaṇa* (etiopathogenesis with clinical presentation) related to *Nidranasa* (disturbance or loss of sleep) will be completed for descriptive and exploratory analysis. Written informed consent will be obtained at this stage. Following the screening visit, participants will attend a baseline assessment session, during which ISI, PSQI, sleep diary orientation, safety checks, completing the clinical evaluation. Screening and baseline visit may occur on the same day if eligibility is confirmed and consent is obtained. Following which a baseline evaluation is done and, participants are randomized into 1:1 groups. Participants in the add- on arm will receive *Siro-pichu* (7 days) and *Padabhyanga* twice daily (14 days) with demonstration, training and home based adherence monitoring, while both groups receive sleep hygiene education and eight twice-weekly sessions of CBT-I delivered by certified psychologists. Sessions will follow a structured CBT-I manual that includes sleep restriction, stimulus control, cognitive restructuring, relaxation training, and relapse-prevention modules. Adherence will be monitored through attendance logs, sleep diaries, DSTED entries, and telephonic check-ins. Upon completion of the intervention period (at Week 4), participants will attend an assessment post-intervention visit to repeat ISI, PSQI, and other outcome measures.

Durability of treatment effects is evaluated during a post-intervention visit (Week 4) and a 3-month follow-up either in person or via telehealth. Throughout the study, participants will remain in active communication with the research team for support, documentation of adherence, and monitoring of any rescue medication use.

### Harms and adverse events monitoring

4.4

Harms will be defined as any untoward medical occurrence, whether or not causally related to the intervention, including adverse events (AEs), adverse reactions, serious adverse events (SAEs), and unexpected events. Adverse events will be systematically recorded using the WHO–UMC (World Health Organization–Uppsala Monitoring Center) causality assessment framework.

#### Monitoring schedule

4.4.1

##### Intervention phase (weeks 0–4)

4.4.1.1

Active AE screening will occur at every in-person or telehealth contact.A structured ADR/AE checklist will be completed weekly.Participants will be specifically asked about new or worsening symptoms.DSTED diary entries include prompts for reporting discomfort or unexpected symptoms.

##### Follow-up phase

4.4.1.2

AE assessment will be conducted at each scheduled follow-up visit.Participants will be instructed to report any adverse events immediately between visits.Monthly structured AE review will be performed during follow-up assessments.

#### Documentation

4.4.2

All AEs will be documented in standardized Case Report Forms including:

Event description.Date of onset and resolution.Severity of the event (mild, moderate, severe).Assessed relatedness to study intervention.Action taken.Outcome.

The Principal Investigator will be evaluating each event for severity and causality.

#### Serious adverse events

4.4.3

Any SAE will be reported to the Institutional Ethics Committee (IEC) within 24 h of awareness Appropriate clinical evaluation, referral and management will be initiated immediately.

In cases where an AE is considered probably or definitely related to the intervention and is of moderate or severe intensity, the intervention will be discontinued for that participant and standard care will be provided. Participants can report issues using emergency contact details provided in the informed consent.

All rescue medications and supportive measures will be documented for outcome interpretation. Due to low risk nature of the trial interventions, no interim harm-related analysis is planned, but continuous safety oversight will be maintained. Participants will be advised to promptly report any discomfort, worsening of insomnia symptoms, headaches, skin irritation, allergic reactions to oils, slips/falls after the intervention or other unexpected physical/ psychological reactions.

### Sample size

4.5

This study is designed as an exploratory randomized controlled trial intended to estimate preliminary between-group differences and assess feasibility parameters rather than to establish confirmatory superiority.

The sample size was estimated using the standard formula for comparison of two independent means:

$$n=\frac{2s_{p}^{2}{\left(Z_{1-\alpha /2}+Z_{1-\beta }\right)}^{2}}{{\left(\mu_{1}\mu_{2}\right)}^{2}}$$

where 
$s_{p}$
 represents the pooled standard deviation, 
$\mu_{1}-\mu_{2}$
 represents the expected mean difference between groups, 
$Z_{1-\alpha /2}$
, 
$Z_{1-\beta }$
 correspond to conventional planning parameters.

The expected post-intervention ISI mean in the intervention group (6.9) was informed by pilot observations in perimenopausal women receiving *Siro-pichu* and *Padabhyanga* with *Ksirabala Taila*. The expected post-intervention ISI mean in the control group (10.9) was derived from Ayabe et al. (49), a multicenter randomized controlled trial evaluating CBT-I in adults with pharmacotherapy-resistant insomnia. Although the Ayabe et al. study included both sexes, the majority of participants were women with a mean age of 52 years, supporting its relevance to the present perimenopausal population (49, 50). The anticipated mean difference between groups was therefore approximately 4 points on the ISI scale. A pooled standard deviation of 4.3 was derived from pilot data. Using a two-sided alpha of 0.05 and 90% power as conservative planning parameters with a 1:1 allocation ratio, the required sample size was estimated at approximately 26 participants per group. Allowing for an anticipated attrition rate of 15%, the final planned sample size was set at 31 participants per arm (total *N* = 62). This calculation was applied as a pragmatic planning tool to avoid underestimation of participant numbers and to permit preliminary effect-size estimation. The study is not powered for confirmatory hypothesis testing, and findings will be interpreted within an exploratory, hypothesis-generating.

### Recruitment

4.6

Recruitment will be facilitated through educational programs, health talks, and distribution of informational posters at community centers and outpatient clinics. This is to attract focus in recognizing difficulty initiating or maintaining sleep, early morning awakening, and non-restorative sleep associated with daytime impairment commonly experienced during the perimenopausal transition. Following these initiatives, preliminary screenings will be conducted using standardized tools, such as the Insomnia Severity Index (ISI), to identify potential participants meeting the study’s symptom profile. Women identified with moderate to severe insomnia symptoms and meeting the preliminary criteria will be invited for a detailed evaluation at the Outpatient Department (OPD) of the Amrita Ayurveda Hospital, Amrita School of Ayurveda, [name].

Recruitment into the study will be contingent upon:

Confirmation of perimenopausal status through clinical history (as per STRAW staging criteria).Fulfillment of all established inclusion criteria.Exclusion of individuals based on predefined exclusion criteria.Completion of the informed consent process.

Only those participants who meet the criteria and provide written informed consent will be enrolled in the trial. Recruitment will continue until the predetermined sample size is achieved.

### Randomization and allocation sequence

4.7

#### Sequence generation

4.7.1

The random allocation sequence will be generated prior to participant enrollment by an independent statistician using R statistical software (version 4.1.5). Block randomization with a fixed block size of 4 will be used to ensure balanced allocation between study arms throughout recruitment. The allocation ratio will be 1:1 (Intervention Group: Control Group). No stratification factors will be applied. The statistician will not be involved in recruitment, intervention delivery, or outcome assessment.

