#### Implementation and blinding

4.7.3

Participant recruitment and eligibility confirmation will be conducted by the Principal Investigator and designated Co-Investigators at the OPD. After completion of baseline assessments and confirmation of eligibility, the investigator will request allocation from the designated trial coordinator. The next sequential envelope will then be opened to reveal group assignment. Due to the nature of the intervention (CBT-I ± Ayurvedic add-on), participants and Ayurvedic intervention providers cannot be blinded.

The following personnel will remain blinded:

CBT-I therapists (will deliver sessions without knowledge of group allocation).Independent outcome assessor (will administer ISI, PSQI, and follow-up measures).Statistician (will analyze anonymized coded datasets).

The Principal Investigator will oversee study conduct and ethical compliance without access to the allocation list. The use of a fixed block size will maintain balance between groups, while the allocation concealment method will prevent selection bias. The independent generation of the randomization sequence will avoid manipulation of group assignments. This structured process ensures allocation concealment until assignment and minimizes selection, performance, and detection bias.

Role of Principal Investigator (PI): The Principal Investigator will oversee protocol conduct and ethical compliance but will not be involved in allocation concealment, intervention delivery, or outcome assessment.

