##### Personnel who cannot be blinded (due to study procedures)

4.7.3.2

Participants: Cannot be blinded because only the intervention group receives visible Ayurvedic therapies (*Siro-pichu* and *Padabhyanga*), while the control group does not.Co-investigators as Ayurvedic intervention providers: Cannot be blinded because they directly administer and train participants in *Siro-pichu* and *Padabhyanga* procedures.Medical Officer/Designated Research Staff: Responsible for maintaining the allocation list, distributing intervention kits (*Kṣirabala Taila*), and ensuring allocation concealment. This person will not be involved in outcome assessment or data analysis. This structured approach ensures rigorous randomization, allocation concealment, thereby maintaining methodological integrity and minimizing potential biases throughout the trial.

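### Fixed, disclosed blocks of 4, with recruiting roles not separated from unblinded training or list-holding, leave the assurance against selection bias unsecured

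*Protocol article*

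**What the plan says.** Section 4.7.1 sets the scheme: "Block randomization with a fixed block size of 4 will be used to ensure balanced allocation between study arms throughout recruitment". It adds "No stratification factors will be applied", and the ratio is 1:1. With a single centre (section 3.1), this gives one running sequence whose block size is in print.

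On recruitment, section 4.7.3 says: "Participant recruitment and eligibility confirmation will be conducted by the Principal Investigator and designated Co-Investigators at the OPD". The investigator then asks the trial coordinator for an allocation, and the next envelope is opened to show the group.

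On delivery, section 3.6.2.1 has a Co-Investigator demonstrate the procedures on Day 0. Section 4.7.3.2 says of Co-Investigators acting as Ayurvedic providers: "Cannot be blinded because they directly administer and train participants".

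On the list, section 4.7.2 has a designated Medical Officer prepare the sealed envelopes. Section 4.7.3.2 describes the Medical Officer or designated research staff as "Responsible for maintaining the allocation list, distributing intervention kits". Both sections bar this person from outcome assessment and from analysis; neither mentions screening. Section 4.3, describing the Week 0 screening, says "the medical officer document demographic details, perimenopausal status (STRAW staging), and chronic insomnia symptoms".

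Section 4.7.3 concludes: "The use of a fixed block size will maintain balance between groups, while the allocation concealment method will prevent selection bias".

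**The concern.** Sealed opaque envelopes hide the next card. They do not hide what the cards already opened imply about it. Anyone who knows that blocks have size 4 and has seen the assignments so far can count what is left in the current block. The one staff group that recruits also contains the people who necessarily learn who is in the add-on arm, and the protocol does not say that they are different individuals.

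The Medical Officer wording raises a separate question. A person who holds the list knows every future assignment. If that person also takes part in screening, concealment depends on conduct rather than on procedure.

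What is at stake is the primary contrast. Some entry conditions need judgement, such as willingness to follow CBT instructions (3.5.1) and lifestyle factors that disturb sleep timing (3.5.2), and the moment of enrolment is open to choice. Participants are unblinded, the ISI is self-completed (4.8.1), and the primary comparison is an unadjusted t-test or Mann–Whitney test (4.9.1). If women with a better outlook were steered to one arm, the difference would appear as a treatment effect.

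**Working it through.** **Inputs.** Fixed block size 4, 1:1, no strata (4.7.1). Total N = 62 (4.5). The protocol gives no figure for predictability, so there is none to reproduce. The N of 62 itself follows from section 4.5: with a difference of 4, SD 4.3, two-sided 5% and 90% power, the t-test calculation gives 25.3, rounded up to 26 per group, and 26/0.85 = 30.6, rounded up to 31 per arm.

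**Assumption.** The recruiter knows the block size and all past assignments. This is the worst case that the text leaves open for a recruiter without the list.

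**Certain foresight.** A block with two of each arm has 6 equally likely orders.
- Positions 1 and 2 are never forced.
- Position 3 is forced when the first two are alike: 2 of 6 orders, or 1/3.
- Position 4 is always forced.
- Expected forced assignments per full block: 1/3 + 1 = 4/3.
- 62 = 15 × 4 + 2, and the two places in the incomplete last block are never forced. Total: 15 × 4/3 = 20 of 62, or 32%.

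**Best guess.** The chance of a correct guess at positions 1 to 4 is 1/2, 2/3, 2/3 and 1.
- Per full block: 0.5 + 0.667 + 0.667 + 1 = 2.833.
- Last two places: 0.5 + 0.667 = 1.167.
- Total: 15 × 2.833 + 1.167 = 43.7 of 62, or 70%, against 50% by chance.

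**What this could do to the estimate (illustration only).** Suppose a recruiter enrols women whose expected ISI change is better by g points when the add-on arm is guessed, and worse by g when control is guessed. The net excess of correct over wrong guesses is 2 × 0.704 − 1 = 0.409. The bias in the between-group difference is 2 × 0.409 × g = 0.82g. For g from 0.5 to 2 (assumed; the documents give no value) this is 0.4 to 1.6 ISI points, against a planned difference of about 4.

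**Effect of varying the block size.** Simulation of 4,000 lists of 62, with an optimal guesser who knows the set of sizes but not their order:

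| Blocks | Known with certainty | Best guess correct |
|---|---|---|
| Fixed 4 | 32% | 70% |
| Random 2/4/6 | 4.1% | 70% |
| Random 4/6 | 5.6% | 69% |
| Random 4/6/8 | 2.2% | 68% |

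Varying sizes removes nearly all certain foresight but hardly lowers the guessing rate. Keeping recruiters away from past assignments therefore matters more than the choice of block sizes.

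**Medical Officer.** Section 4.3 gives screening documentation to the medical officer. Sections 3.4 and 4.7.3 give eligibility to the Principal Investigator and Co-Investigators. Sections 4.7.2 and 4.7.3.2 give the envelopes and list to a Medical Officer. Nothing in these sections rules out that the officer who documents screening is also the list-holder.

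**The case against.** The sequence is generated by an independent statistician and carried in sequentially numbered, opaque, sealed envelopes, which is sound practice. ISI 8 to 21 and PHQ-9 are numeric cut-offs, which narrows discretion. The Principal Investigator is said to have no access to the list. The trial is declared exploratory throughout. Imbalance in measured baseline ISI could be adjusted for.

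A reader might infer that the same Co-Investigators recruit and train, and that the screening medical officer is the list-holder and so foresees every assignment. The documents do not support either inference. The title of Co-Investigator covers several duties, including a blinded outcome assessor (4.7.3.1), so a shared title does not show a shared person. Section 4.3 only has the medical officer document details; the eligibility decision lies elsewhere. Complete foresight would require that the list-holder both is that officer and influences enrolment, and neither is stated.

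These points limit the concern but do not remove it. Envelopes do not stop deduction from past assignments, and lack of the list does not stop an investigator from following the sequence. Adjustment for baseline ISI would not reach motivation or expectancy. The exploratory label does not help either, because the intended product is an effect estimate to guide later trials, and selection bias distorts estimates as much as tests.

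**Conclusion.** The concern holds as a gap in the written procedure. With fixed, disclosed blocks of 4 and no stated separation of recruiting from training, a recruiter who knows past assignments could foresee 20 of 62 allocations (32%) and guess about 70% correctly. Those figures rest on full knowledge of past assignments, which the text permits but does not establish. The Medical Officer sections leave it open whether the list-holder takes part in screening, and must be reconciled. The statement that concealment will prevent selection bias promises more than the procedure delivers. Any bias in the ISI difference depends on steering that cannot be known, so the range of 0.4 to 1.6 points is only illustrative. Severity: should be fixed.

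**What to change.** 1. Generate the list, or its unused part if enrolment has begun, in randomly varying blocks, for example 4, 6 and 8, with the sizes withheld from site staff. Certain foresight falls to about 2% and the best guess to about 68%. Blocks of 2 are better left out, since with them the guessing rate stays at 70%.
2. In section 4.7.3, state that Co-Investigators who recruit and confirm eligibility are not those who train add-on participants, and that recruiters are not told past assignments.
3. In sections 4.7.2 and 4.7.3.2, state that the Medical Officer who holds the list and envelopes takes no part in screening or eligibility. Reconcile section 4.3 with sections 3.4 and 4.7.3.
4. In section 4.7.3, replace the claim of prevention with one that the method reduces the risk of selection bias.

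The cost is one new run of the list in R, a wording amendment for the ethics committee, and a division of duties among existing staff. With blocks of 4, 6 and 8 the final split is usually no worse than 32:30 and rarely 33:29 (four of one arm opening an incomplete last block of 8), which is negligible for precision.

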#### Allocation concealment mechanism

4.7.2

Based on the randomization list, a designated Medical Officer not involved in outcome assessment or statistical analysis will prepare sequentially numbered, opaque, sealed envelopes (SNOSE). Each envelope will contain a card specifying the group allocation. Envelopes will be stored in a locked cabinet within the study office and opened sequentially in strict numerical order. The intervention codes will only be revealed after the completion of all post-intervention assessments or earlier in the event of a medical emergency that requires unblinding.

#### Implementation and blinding

4.7.3

Participant recruitment and eligibility confirmation will be conducted by the Principal Investigator and designated Co-Investigators at the OPD. After completion of baseline assessments and confirmation of eligibility, the investigator will request allocation from the designated trial coordinator. The next sequential envelope will then be opened to reveal group assignment. Due to the nature of the intervention (CBT-I ± Ayurvedic add-on), participants and Ayurvedic intervention providers cannot be blinded.

The following personnel will remain blinded:

CBT-I therapists (will deliver sessions without knowledge of group allocation).Independent outcome assessor (will administer ISI, PSQI, and follow-up measures).Statistician (will analyze anonymized coded datasets).

The Principal Investigator will oversee study conduct and ethical compliance without access to the allocation list. The use of a fixed block size will maintain balance between groups, while the allocation concealment method will prevent selection bias. The independent generation of the randomization sequence will avoid manipulation of group assignments. This structured process ensures allocation concealment until assignment and minimizes selection, performance, and detection bias.

Role of Principal Investigator (PI): The Principal Investigator will oversee protocol conduct and ethical compliance but will not be involved in allocation concealment, intervention delivery, or outcome assessment.

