#### Adherence to Ayurvedic regimen

3.9.1

Adherence to *Siro-pichu* and *Padabhyanga* will be defined as completion of at least 80% of the prescribed applications during the intervention phase.Completion will be recorded in the Daily Sleep and Treatment Engagement Diary and reviewed during weekly follow-ups.Random tele-supervision (10% of participants) will be conducted to support procedural fidelity.

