##### The following personnel will remain blinded throughout the trial

4.7.3.1

CBT-I psychologists: Will deliver all CBT-I sessions using a standardized manual without being informed of whether the participant is in the intervention or control group.Independent Outcome assessor (Co-investigator): Will conduct ISI, PSQI, sleep diary review, and follow-up assessments while blinded to the allocation to minimize assessment bias.Statistician: Will perform data analysis using coded datasets. Unblinding will occur only after completion of the final statistical analysis.

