#### Data collection procedures

4.8.1

Study data will be captured via standardized paper-based case record forms (CRFs) and validated outcome instruments. Trained research staff, independent of intervention delivery, will oversee data collection at the Outpatient Department (OPD) during screening and baseline. Subsequent intervention (Weeks 2, 4) and follow-up (Weeks 6–16) assessments will occur in person or via telehealth. Outcome instruments (ISI, PSQI, SDS, DSTED) are self-administered by participants under supervision of trained research staff independent of intervention delivery. Research staff may clarify instructions but will not influence responses (Table 1).

**Table 1 tab1:** Data collection methods.

Trial instrument	Purpose	Frequency of measurement	Timepoints of assessment
Insomnia Severity Index	To determine the primary outcome: severity of insomnia symptoms over the preceding two weeks	Every 2 weeks	Baseline (Week 0), Week 2, Week 4 (end of intervention), Week 6, Week 8, Week 12, Week 14, Week 16 (end of follow-up)
Pittsburgh Sleep Quality Index	To evaluate the overall sleep quality and its domains, including latency, duration, efficiency over the past month	Monthly	Baseline (Week 0), Post- treatment (Week 4), Follow-up Months 1, 2, and 3
ADR Monitoring Checklist	To identify and document any adverse events or reactions related to the integrative intervention	Ongoing monitoring at each contact point	Weekly during intervention (Weeks 0– 4), and monthly during follow-up (Months 1–3)
Severity of dependency Scale	To detect any signs of behavioral or psychological dependency on *Śiro-pichu* and *Pādābhyanga* therapies	Twice during the study	Post-intervention (Week 4), End of follow-up (week 16)
Daily Sleep and Treatment Engagement Diary	To assess adherence and consistency in following the prescribed intervention protocol	At the end of intervention and follow up	Week 4 of intervention, Week 16 of follow up

Official Malayalam versions of ISI and PSQI were obtained from ePROVIDE–MAPI Research Trust (COA request submitted 08-Aug-2025; approval date: 01 September 2025). Instruments will be administered in accordance with licensing terms. Table 1 shows the data collection methods in detail.

Sleep diaries will record total sleep time (TST). For descriptive summaries, TST will be categorized as optimal (7–9 h), short (<6 h), or long (>9 h). Classification is for characterization only and will not determine treatment response.

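### Assessor blinding cannot support the claim that detection bias is minimized, because ISI and PSQI are rated by participants who know their arm

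*Protocol article*

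**What the plan says.** Section 4.7.3 (Implementation and blinding) closes its description of randomization and blinding with "This structured process ensures allocation concealment until assignment and minimizes selection, performance, and detection bias". Among the blinded personnel it lists the "Independent outcome assessor (will administer ISI, PSQI, and follow-up measures". Section 4.7.3.1 identifies this person as a co-investigator and gives the duties and their purpose: "Will conduct ISI, PSQI, sleep diary review, and follow-up assessments while blinded to the allocation to minimize assessment bias". CBT-I psychologists and the statistician are also to be blinded.

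Section 4.8.1 (Data collection procedures) describes how the scores arise: "Outcome instruments (ISI, PSQI, SDS, DSTED) are self-administered by participants under supervision of trained research staff independent of intervention delivery". Of those staff it says: "Research staff may clarify instructions but will not influence responses".

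Section 4.7.3.2 is plain about the respondents: "Participants: Cannot be blinded because only the intervention group receives visible Ayurvedic therapies". Section 3.1 explains that no sham oleation was used, partly because oil applied to scalp or feet would probably have expectancy effects of its own. Section 6 (Limitations) names the missing sham, the lack of actigraphy, rescue medication and the unvalidated use of the SDS. It does not mention self-report by unblinded participants.

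**The concern.** Detection bias enters where the outcome is judged. For the ISI and PSQI that judgment is the participant's own, and she knows whether she received the oil procedures. A blinded supervisor can avoid steering her answers but cannot remove her knowledge of her arm. The safeguard the article cites therefore does not act on the risk it is said to minimize.

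The trial exists to find out whether there is a signal that justifies a larger study, and its effect estimate is what that study would inherit. A reader who accepts section 4.7.3 would take an ISI difference as protected against differential reporting when it is not. Section 6 does not correct this: it presents the missing sham as a problem of separating tactile, sensory and specific effects, which is a different matter from reporting bias.

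**Working it through.** **Passages side by side**

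| Question | What the article says | Where |
|---|---|---|
| Which biases are said to be minimized? | Selection, performance and detection | 4.7.3 |
| What is the safeguard against assessment bias? | A blinded co-investigator who conducts ISI and PSQI | 4.7.3.1 |
| Who produces the ISI and PSQI scores? | The participant, with staff only clarifying instructions | 4.8.1 |
| Does she know her arm? | Yes | 4.7.3, 4.7.3.2 |
| Is there a sham? | No, and expectancy effects are thought likely | 3.1 |
| Is unblinded self-report listed as a limitation? | No | 6 |

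For detection bias, rows 3 and 4 settle the matter: the rater is unblinded, whoever hands over the form.

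For performance bias, the CBT-I common to both arms is delivered by blinded therapists, which is real but partial protection. Only one arm has the Day 0 demonstration, the oil kits, the reminders during the Ayurvedic regimen and up to 14 days of home procedures (sections 3.6.2, 3.6.2.1, 3.9.3, 4.7.3.2), and its providers are unblinded.

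**Assessor exposure**

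The documents leave this open.

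- The assessor is a co-investigator (4.7.3.1), and so are the Ayurvedic providers (4.7.3.2). Nothing states outright that they are different people.
- The assessor gives unspecified follow-up measures. The SDS, taken at Weeks 4 and 16, is aimed at dependency on the two oil procedures (Table 1).
- The DSTED logs the oil applications: "Completion will be recorded in the Daily Sleep and Treatment Engagement Diary and reviewed during weekly follow-ups". It is reviewed at each contact (4.8.2), with no reviewer named.

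**The planning figure**

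Section 4.5 gives a difference of 4, SD 4.3, two-sided alpha 0.05, power 90% and attrition 15%.

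- n = 2 × 4.3² × (1.960 + 1.282)² / 4² = 24.29, so 25 per arm by the normal formula. The t-based calculation gives power 0.897 at 25 and 0.908 at 26, so 26, as stated.
- 26 / (1 − 0.15) = 30.6, so 31 per arm, as stated.

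**Illustration only**

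The documents give no size for reporting bias. Against the planned 4 points, an assumed differential of 1 or 2 points is 1/4 = 25% or 2/4 = 50%.

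Now suppose there is no true effect, SD 4.3 applies to the analyzed change, and self-report shifts by b points more in one arm than in the other. The standard error is 4.3 × √(2/n), which is 1.193 at 26 per arm and 1.092 at 31. The chance of p < 0.05 comes from a noncentral t with 2n − 2 degrees of freedom and noncentrality b/SE. For b = 2 the noncentrality is 1.68 at 26 per arm and 1.83 at 31.

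| Differential shift b (ISI points) | 26 per arm | 31 per arm |
|---|---|---|
| 0 | 5% | 5% |
| 0.5 | 7% | 7% |
| 1 | 13% | 15% |
| 1.5 | 24% | 27% |
| 2 | 38% | 44% |
| 3 | 69% | 77% |

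**The case against.** The strongest reply is that nothing is hidden. Section 4.7.3 speaks of minimizing bias, not eliminating it, and itself says participants and Ayurvedic providers cannot be blinded. The missing sham and the lack of objective sleep measures are disclosed, expectancy is mentioned in section 3.1, and the trial disclaims confirmatory efficacy throughout. This stands as a defense of the open design, which is not at issue. It does not rescue a sentence crediting the process with control of detection bias, because the measure cited does not act on the person giving the rating.

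Three stronger readings are tempting, and the documents do not support them.

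- A reader might see a flat contradiction between an assessor who administers the scales and participants who self-administer them. The passages can be read together, since a blinded staff member can supervise a form that the participant completes. What remains is that sections 4.7.3 and 4.7.3.1 never say the rating is self-report.
- A reader might infer that the assessor treats add-on participants or handles forms that reveal the arm. No passage says so. The assessor is called independent, co-investigators are plural, section 4.8.1 keeps supervising staff apart from intervention delivery, and section 8.6 limits assessors to what their role needs. The assessor's sleep diary review need not mean the DSTED, because section 4.3 lists sleep diaries and DSTED entries separately. Exposure is not ruled out, which supports a clarification but not a finding that blinding fails.
- A reader might suppose that any expectancy effect adds in full to the ISI difference. Both arms receive active CBT-I with expectations of its own, so only the part that differs between arms biases the estimate.

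**Conclusion.** The point holds in a limited form. For the ISI and PSQI, in all 62 planned participants, the statement that detection bias is minimized has no support in the design described. For performance bias it holds only as far as blinded CBT-I delivery reaches. It would go too far to call the whole sentence false: its parts on allocation concealment and selection bias are not touched here.

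The size of the bias cannot be estimated from the documents. The 1 to 2 point shift and the table of probabilities rest on an assumed differential, no true effect and SD 4.3. They show only that a modest shift could look like the signal being sought. The conclusion does not depend on them. It rests on three things the article states: the ratings are self-completed, the raters know their arm, and there is no sham. No sample size or analysis changes. What changes is how an ISI difference may be read.

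**What to change.** 1. In section 4.7.3, limit the claim to selection bias and allocation concealment, and add that blinding the CBT-I therapists limits performance bias only in part.
2. Bring sections 4.7.3 and 4.7.3.1 into line with 4.8.1: ISI and PSQI are self-reported by unblinded participants, and the person supervising completion is blinded. Say whether that person is the co-investigator of 4.7.3.1 or the research staff of 4.8.1.
3. In section 6, add that a between-arm difference in ISI or PSQI may include differential expectancy or reporting bias.
4. As a precaution, state that the assessing co-investigator does not train or treat add-on participants, and assign DSTED, SDS and deviation-form handling to existing staff who need not be blinded. Because the SDS and DSTED are outcome instruments, those staff should still meet the independence condition in 4.8.1. The Medical Officer is barred from outcome assessment by 4.7.3.2, so could not take on these instruments as the text stands.

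Items 1 to 3 cost a few sentences. Item 4 costs some reassignment of tasks among existing staff and needs no new personnel.
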